#### Analysis

Log-binomial regression will allow direct estimation of risks and risk ratios (i.e. relative risks) on each outcome. The model will be adjusted with intervention (yes vs. no) and time (baseline, 12 and 24 month) as categorical data where baseline is set as reference and interaction between intervention and time. The model will be adjusted with the intervention (yes or no) and with a random centre effect. Chi-square test and 95% confidence intervals (CI) will be computed.

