### The treatment of cardiovascular risk in primary care using electronic decision support (TORPEDO) study

There have been few randomised evaluations of QI interventions in the Australian primary healthcare setting. We designed a multifaceted QI intervention for CVD risk management in Australian primary healthcare. The intervention drew on two established QI mechanisms: 1) electronic decision support and 2) audit and feedback (summary of the clinical performance over a specified period of time) [32-37]. The intervention was evaluated in the TORPEDO study, a cluster-randomised controlled trial (cRCT) involving 60 health services. Details of the trial are published elsewhere [38]. In brief, the system was integrated with the healthcare provider’s EHRs, and included (1) a real-time decision support interface using an algorithm derived from several evidence based national guidelines (Figure 1); (2) a patient risk communication interface which included ‘what if scenarios’ to show the benefits from particular health risk factor improvement during a consultation (Figure 2); (3) an automated clinical audit tool for extraction of data and review of health service performance (Figure 3); and (4) a web portal where services can view peer-ranked performance over time (Figure 4). Healthcare providers could use the point-of-care tool as part of a routine clinical consultation. For the audit and feedback component, quality indicators were developed for patients who had visited the health service at least three times in the preceding 2 years and once in the preceding 6 months. The population studied was based on national guideline recommendations for CVD risk screening and included Aboriginal and Torres Strait Islander people over 35 years and all others over 45 years [38].

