**Quality improvement portal.**

Data were collected for 38,725 people from the 60 health services. Overall, when compared with control, the intervention was associated with a 25% relative (10% absolute) improvement in CVD risk factor screening. Overall, there was no significant difference in the prescribing rates of recommended medicines to people at high CVD risk. The intervention was, however, strongly associated with improvements in the sub-group at high CVD risk that was not prescribed with recommended medicines at baseline. There were also improvements in intensification of existing, recommended medication regimens. There were modest improvements in attaining blood pressure targets but no differences in other clinical outcomes. The improvements in recommended prescriptions to high risk patients were not accompanied by increased prescribing rates for patients at low risk [39].

Although the intervention exhibited significant improvements in some outcomes, it remains unclear how this intervention was actually used in practice and what factors promoted and hindered its use. Answers to these questions are critical in order to inform future directions for its implementation and for implementation of similar interventions in other settings.

In this paper, we outline our protocol for a theory-based process evaluation of the TORPEDO intervention. The broad objectives are to understand how, why, and for whom the intervention produced the observed outcomes and to develop effective strategies for translation and dissemination. The evaluation will identify which intervention components promoted or had minimal impact at the provider, patient, and system levels and the mechanism of change. It will also identify the contextual influences on the delivery of the intervention and its outcomes. The specific objectives are the following:To understand whether intervention effects are sustained in a post-trial setting;To identify implementation barriers and enablers;To understand how CVD risk is communicated in the doctor/patient interaction both with and without the use of the intervention; andTo identify cost considerations for delivering the intervention at scale in the Australian primary healthcare system.

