#### Methods

At the end of study follow-up visit for the TORPEDO study, all 60 health services have the option to either continue the use of the intervention or have the intervention implemented for use in the usual care health services for an additional 12 months. A post-trial clinical audit data extraction at minimum of 24 months from baseline will be conducted for the health services expressing interest to use the intervention. The objective of this study is to assess the impact of the use of the intervention over time on the two primary outcomes: (1) proportion of CVD risk factor screening and (2) proportion of appropriate medication prescription in the high risk individuals for the intervention arm and usual care arm at post-end of study following baseline.

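### Study 1 models three extractions from the same services with one random centre effect, so the intervention-by-time standard errors are not valid in general: probably too small for screening, of uncertain direction for prescribing

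*Protocol article*

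**What the plan says.** The Analysis paragraph of Study 1 in the protocol article fixes the following:

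- **Model family.** "Log-binomial regression will allow direct estimation of risks and risk ratios".
- **Fixed effects.** Intervention and "time (baseline, 12 and 24 month) as categorical data where baseline is set as reference and interaction between intervention and time".
- **Correlation structure.** "The model will be adjusted with the intervention (yes or no) and with a random centre effect".
- **Inference.** "Chi-square test and 95% confidence intervals (CI) will be computed".

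It names no service-by-time term, patient term or robust variance.

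Other sections bear on the point:

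- The Background reports the size of the completed trial: "Data were collected for 38,725 people from the 60 health services".
- The TORPEDO section defines the audit-and-feedback population by recent attendance: patients who had "visited the health service at least three times in the preceding 2 years and once in the preceding 6 months".
- The Study 1 Methods say that the post-trial extraction "will be conducted for the health services expressing interest to use the intervention", so it may cover fewer than 60 services.
- The same Methods name two outcomes: risk factor screening, and appropriate prescribing among people at high risk.

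**The concern.** The intervention-by-time terms answer objective 1, whether the effects are sustained after the trial. They are contrasts of change within the same services. A single exchangeable centre effect assumes that two patients of one service are as strongly correlated 24 months apart as within one extraction. Such an effect largely cancels from a within-service change, which is then judged against patient-level noise alone.

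The protocol itself expects services to change differently. Each service chooses whether to continue or take up the tool after the trial (Study 1 Methods). Cases are sampled to differ as widely as possible in the trial outcomes (Study 3 Methods). The Discussion describes uneven success and complicated patterns of use. The stated model has no term for this variation.

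The model also gives no extra correlation to patients who recur. If the extractions use the attendance rule, many patients would appear more than once. Ignoring their correlation inflates the standard error of a change.

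The two faults therefore pull in opposite directions and need not cancel. Where the first dominates, chance drift among services could be read as a sustained or lost effect. Where the second dominates, precision is understated and a real change could be missed.

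**Working it through.** The article states no sample size, power, ICC or standard error for Study 1, so there is no figure of its own to reproduce. The check compares the true standard error of a change contrast with the one that the stated model would report.

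**Inputs from the article**
- 60 services and 38,725 people (Background): 38,725/60 = 645 per service. These are the completed trial's numbers; the 24-month figures are unknown.

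**Assumed inputs (the article gives none)**
- ICC within a service and extraction: 0.01 to 0.05.
- Between-period correlation of the service effect (CAC): 0.95 to 0.8.
- Net within-patient correlation across extractions, r: 0 or 0.5. This is overlap times correlation, so 0.5 stands for strong recurrence.
- High-risk patients: 30% of 645, about 194 per service.

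**Formula.** With total variance 1 and m patients per service and extraction, the variance of a change is proportional to

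- truth: ICC(1 − CAC) + (1 − r)(1 − ICC)/m
- stated model: (1 − ICC)/m

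so that (SE ratio)² = (1 − r) + m × ICC × (1 − CAC)/(1 − ICC).

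The actual error rate of a nominal 5% test is 2 × [1 − Φ(1.96/ratio)]. The mildest corner is ICC 0.01 with CAC 0.95. The most severe is ICC 0.05 with CAC 0.8.

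**Screening, m = 645**
- Mildest: the drift term is 645 × 0.0005/0.99 = 0.326.
  - r = 0: √1.326 = 1.15; error rate 8.9%.
  - r = 0.5: √0.826 = 0.91; error rate 3.1%.
- Most severe: the drift term is 645 × 0.010/0.95 = 6.79.
  - r = 0: √7.79 = 2.79; error rate 48%.
  - r = 0.5: √7.29 = 2.70; error rate 47%.

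**Prescribing, m = 194 (assumed)**
- Mildest: the drift term is 194 × 0.0005/0.99 = 0.098.
  - r = 0: √1.098 = 1.05; error rate 6.1%.
  - r = 0.5: √0.598 = 0.77; error rate 1.1%.
- Most severe: the drift term is 194 × 0.010/0.95 = 2.04.
  - r = 0: √3.04 = 1.74; error rate 26%.
  - r = 0.5: √2.54 = 1.59; error rate 22%.

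**Where the direction turns.** The ratio is 1 when 1 − CAC = r(1 − ICC)/(m × ICC). With r = 0.5:
- Screening: CAC = 0.985 at ICC 0.05 (0.475/32.25 = 0.015) and 0.923 at ICC 0.01 (0.495/6.45 = 0.077). Below these values the model's standard error is too small.
- Prescribing: CAC = 0.951 at ICC 0.05 (0.475/9.7 = 0.049) and 0.745 at ICC 0.01 (0.495/1.94 = 0.255). Over the CAC range 0.8 to 0.95 the model's standard error is therefore too small at ICC 0.05 and too large at ICC 0.01.

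With no service-by-time variation at all (CAC = 1) and r = 0.5, the ratio is √0.5 = 0.71 for either outcome, and the model is clearly conservative.

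**The case against.** **The direction is not known.** A reader might infer that the standard errors are usually much too small. The documents do not support that in general. None of ICC, CAC, patient overlap or the high-risk count is given, and the two omissions offset each other. This stands. Even for screening, the mildest corner with r = 0.5 gives 0.91, and for prescribing the sign depends on the ICC.

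**The chi-square test.** A reader might also infer a Pearson test on pooled patients that ignores clustering altogether. The sentence closes a paragraph wholly about the regression model, and the natural reading is a test from that model. Nothing in the article describes a pooled test, so no fault is found there.

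**The article is condensed.** It says a random centre effect, not an intercept alone, and a fuller plan could add random slopes or a robust variance. This stands in part: such an extension is possible. But the article chooses to state the correlation structure, and as stated it is a single centre effect. The point concerns a stated choice, not a detail left out.

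**The inputs are borrowed.** The 645 per service comes from the completed trial, while the 24-month extraction covers only interested services. This stands as a limit on the numbers. The ratio depends on patients per service rather than on the number of services, so fewer services would not by itself change it. It would make a small-sample correction more important.

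**Study 1 is a follow-up within a process evaluation,** not the main analysis of the trial. This stands and lowers the severity.

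**Conclusion.** The point holds in a limited form. The stated random structure leaves out service-by-time variation and repeat-patient correlation, so the standard errors of the intervention-by-time terms are not valid in general.

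For screening they are probably too small. Under the assumed ranges the ratio falls below 1 only when a low ICC goes with high CAC and strong patient recurrence, or when CAC is nearly perfect. For prescribing in the smaller high-risk group, the error may run either way. The ratios and error rates are conditional on assumed correlations and on about 645 or 194 patients per service; they are not estimates for this study. Severity: should be fixed.

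**What to change.** Change the correlation structure in the Study 1 Analysis paragraph in one of two ways:

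- Keep the mixed model and add a random service-by-time effect. Add a patient effect as well if the de-identified records can be linked across extractions. The article does not say whether they can.
- Use a log-link Poisson GEE with standard errors clustered by service and a small-sample correction. It still estimates risk ratios, needs no patient linkage, and covers both omissions at once because all of a service's records fall in one cluster.

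The second is the simpler choice if linkage is in doubt. The correction matters because the services with 24-month data may number fewer than 60.

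The cost is a change of wording: the Trial status section reports that quantitative analysis has not begun. Confidence intervals for screening will generally be wider. Those for prescribing may move either way.

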### Study 2: Multilevel modelling study (objective 2)

#### Aim

To determine what patient and health service level variables correlate with the trial outcomes.

#### Methods

Patient variables (age, gender, ethnicity, history of CVD, and diabetes) will be obtained from the automated clinical audit tool, and health service level variables will be collected through Team Climate Inventory (TCI) and Warr-Cook-Wall job satisfaction surveys, customised for use with general practices (GPs) and Aboriginal Community Controlled Health Services (ACCHSs), administered to all general practitioners and other practice and health service staff at the participating 60 sites [56,57]. In addition, health service characteristics such as service size, participation in quality improvement programs, and type of primary healthcare (GP verses ACCHS) will be collected at randomisation.

#### Analysis

TCI is a 44-item questionnaire, and items are rated on a 5-point scale [56]. Job satisfaction is a 15-item questionnaire, and items are rated on a 7-point scale [57]. Multilevel regression model analysis will be conducted to evaluate the influence of team climate and job satisfaction on the primary study outcomes, controlling for patient’s age, gender, practice size, type of PHC, and participation in quality improvement programs. The results will be interpreted within the context of the three conceptual perspectives to better understand what health service factors (if any) are important drivers of use of the intervention in routine practice.

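### The stated Study 2 model names neither randomised arm nor an arm interaction, so its coefficients can show correlates of performance but not which service factors modify the intervention's effect

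*Protocol article*

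**What the plan says.** The aim of Study 2 is "To determine what patient and health service level variables correlate with the trial outcomes". Its Methods section has the Team Climate Inventory (TCI) and the job satisfaction survey "administered to all general practitioners and other practice and health service staff at the participating 60 sites". The parent study was "a cluster-randomised controlled trial (cRCT) involving 60 health services", so the surveys cover both arms.

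The Analysis section says "Multilevel regression model analysis will be conducted to evaluate the influence of team climate and job satisfaction on the primary study outcomes". Arm does not appear in the list of adjustment variables that it then prints, which reads "controlling for patient’s age, gender, practice size, type of PHC, and participation in quality improvement programs". The Study 1 Methods section lists the two primary outcomes: "1) proportion of CVD risk factor screening and (2) proportion of appropriate medication prescription in the high risk individuals". Both can be measured in either arm, and neither measures use of the tool.

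The Analysis section closes by saying that the results, read through three conceptual perspectives, should help to understand "what health service factors (if any) are important drivers of use of the intervention in routine practice". Study 2 is assigned to objective 2, which concerns implementation barriers and enablers.

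**The concern.** Usual-care services are offered the intervention only after the trial (Study 1, Methods), so their trial outcomes arose without it. If sites from both arms are analysed together with no arm term, the climate coefficient averages two quantities: how climate relates to ordinary care, and how it relates to care when the tool is available. Only the difference between these bears on whether climate changes what the intervention achieves.

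The evaluation's overall objective includes finding out for whom the intervention worked, which is a question about effect modification. Study 3 draws Study 2 data into its case analysis. A coefficient that reflects only generally better-run services could therefore be carried forward as evidence of an enabler. Conversely, a factor with opposite associations in the two arms could be missed.

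A lesser point is that the Background reports a 10-point absolute arm effect on screening. A model without arm leaves that effect in the unexplained between-site variation.

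**Working it through.** The article states no sample size, power or significance level for Study 2, so there is no figure to reproduce. The check is a reading of the stated model, followed by an illustration.

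**Reading.**
- Sites: all 60, with no restriction to the intervention arm.
- Outcomes: screening and prescribing.
- Exposures: team climate and job satisfaction.
- Covariates: patient age and gender, practice size, service type, and quality improvement participation.
- Not named: arm, any arm interaction, any measure of use.
- By contrast, the Study 1 analysis names intervention, time and their interaction.

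**What a pooled slope estimates.** Let climate be standardised and unrelated to arm, with slope b_I in intervention sites, b_C in usual care, and a fraction p of sites in the intervention arm. A model without arm then estimates

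pooled slope = p·b_I + (1 − p)·b_C.

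The interaction is b_I − b_C. One weighted average cannot recover the difference, whatever the values of p and the slopes.

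**Illustration.** From the article: 60 sites and a 10-point arm effect on screening. That effect is 25% relative, so usual care is about 0.10/0.25 = 40%. Assumed, because the article does not give them: a 30:30 split, a between-site residual SD of 12 points, and the slopes below. A site-level simulation of 4,000 replicates per scenario gives, in percentage points per SD of climate:

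| Scenario | b_C | b_I | Pooled slope, no arm term | Arm × climate |
|---|---|---|---|---|
| Same in both arms | 5 | 5 | 5.0 | 0.0 |
| Intervention arm only | 0 | 10 | 5.0 | +10.0 |
| Usual care only | 10 | 0 | 5.0 | −10.0 |
| Opposite | −5 | +5 | 0.0 | +10.0 |

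Three incompatible explanations give the same pooled slope, and the fourth gives none. The interaction separates equal slopes from the other three scenarios and shows the direction of the difference.

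**Precision.** With residual SD σ and 30 sites per arm, the standard error is about σ·√(1/60) for the main effect and σ·√(1/30 + 1/30) = σ·√(4/60) for the interaction. The ratio is √4 = 2. At σ = 12 points these are about 1.5 and 3.1 points.

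**Cost of leaving arm out.** A 10-point arm effect with equal allocation adds variance 10² × 0.5 × 0.5 = 25. At σ = 12 the residual SD becomes √(144 + 25) = 13.0, so the standard error of the climate slope rises by 13/12, about 8%. This loss is minor beside the problem of interpretation.

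**The case against.** The strongest reply is that this is a condensed article. Arm is the design variable of the trial, and how it enters the model could be left to an analysis plan. The text never says main effects only; that is inferred from a covariate list. Study 1 had to name arm because it estimates the arm effect over time, so the contrast between the two sections is suggestive and not conclusive. The stated aim is correlation, which the model can deliver. The closing sentence is hedged, and Study 3 asks staff directly why they did or did not use the tool, in cases identified by arm.

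Much of this stands. A reader might infer that arm has been deliberately excluded, or that implementation recommendations will rest on the Study 2 coefficient alone. The article says neither. A reader might also conclude that Study 2 fails its purpose, but the aim of finding correlates can still be met.

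What does not fall away is that the article prints a specific adjustment set without arm and ties the result to drivers of use. Followed as written, that model does not support the inference. This is more than an unstated detail.

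**Conclusion.** The point holds at moderate severity. The stated model can identify correlates of trial outcomes. It cannot distinguish a general correlate of performance from a factor that modifies the intervention's effect. That conclusion follows from the form of the model and does not depend on the assumed slopes, residual SD or allocation. The figures in the table and the factor of two in standard error do depend on assumptions, the latter on roughly equal allocation.

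Three stronger readings are not supported:
- **That pooling halves a true modifier.** This holds only with a zero slope in usual care and equal allocation, and the documents give neither.
- **That an arm interaction would reveal drivers of use.** It would show modification of the effect on screening or prescribing. Drivers of use need a measure of use within intervention sites.
- **That the evaluation cannot proceed without this change.** Study 2 is one observational part of a process evaluation, and the trial's own reported results do not depend on it.

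**What to change.** Add randomised arm to the Study 2 model, with arm × TCI and arm × job-satisfaction terms. Report these interactions with 95% CIs and label them exploratory estimates of effect modification. Take the pooled climate and satisfaction effects from the model with arm but without interactions, because once an interaction is included the climate coefficient is the slope in the reference arm only. Describe the pooled effects as correlates of performance.

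Reword the closing sentence of the Analysis section so that neither term is read as a driver of use. Limit claims about use to intervention-arm data and the Study 3 findings.

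Keep to these two interactions. Extending them to service type, size and quality improvement participation would give 5 factors × 2 outcomes = 10 interaction estimates on 60 clusters, against 2 × 2 = 4 here.

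The cost is a few model terms and a change of wording. Arm is already known for every site, no data need collecting, and the Trial status section says quantitative analysis has not begun. The drawback is imprecision: with 60 clusters and about equal allocation, the interactions have about twice the standard error of the main effects. A wide interval should not be read as evidence of no modification.

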## Discussion

Addressing the challenges of CVD burden requires implementation strategies for increasing the uptake of well-established evidence into practice. Our attempt to address this with a multifaceted QI intervention was moderately but not uniformly successful, suggesting the need for a rigorous process evaluation to understand how and in what ways it was taken up in practice. Such evaluations are crucial to understanding how implementation strategies should be applied in non-trial settings.

Multifaceted interventions, by their nature, invariably lead to complex usage patterns which can make interpretation of study outcomes difficult. In order to maximise understanding that is relevant to other settings, process evaluation is therefore critical. The strength of our process evaluation is its multicomponent, multi-theory approach combining diverse study designs to make sense of how this particular knowledge translation strategy was adopted into practice. Further, by examining implementation from multiple perspectives (provider, patient, health services, and system) the findings are expected to provide both micro- and macro-system perspectives which will be of interest to policy makers and implementers. There are two key limitations to our approach (1) the majority of the data collection will occur toward the end of the trial and in the post-trial phase and may miss critical insights gained from early phase adoption processes; and (2) the study setting is limited to Australian primary healthcare settings and therefore may be only of relevance to health systems with similar contexts, financing, workforce structures, and adoption of electronic medical records.

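### Study 2 words its analysis of team climate and job satisfaction as influence, but states no pre-intervention survey and does not list trial arm as a covariate, so the plan as written supports association only

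*Protocol article*

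**What the plan says.** Study 2 states its aim as follows: "To determine what patient and health service level variables correlate with the trial outcomes". The Abstract also speaks only of correlates. The Analysis section goes further. A multilevel regression will "evaluate the influence of team climate and job satisfaction on the primary study outcomes", and the results will be used to understand "what health service factors (if any) are important drivers of use of the intervention in routine practice".

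The scores come from the Team Climate Inventory (TCI) and a job satisfaction questionnaire, "administered to all general practitioners and other practice and health service staff at the participating 60 sites". No date is attached to either survey. The next sentence of the Methods adds service characteristics and does date those: service size, participation in quality improvement programs and "type of primary healthcare (GP verses ACCHS) will be collected at randomisation".

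The listed covariates are patient age and gender, practice size, type of service and participation in quality improvement programs. Trial arm is not in the list, nor is an earlier survey score. The one general statement on timing is a limitation in the Discussion: "the majority of the data collection will occur toward the end of the trial and in the post-trial phase". The consequence drawn there is that the evaluation "may miss critical insights gained from early phase adoption processes".

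**The concern.** To call a service factor an influence on an outcome, one needs at least to know that it was measured before the outcome, or that the outcome and the treatment could not have changed it. The article does not establish this for climate or satisfaction. Intervention services were given decision support, audit tools and monthly peer-ranked performance feedback. A team that sees itself ranked high or low each month may come to rate its climate and its work differently. A score taken late could therefore be a consequence of the intervention or of the site's results.

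Study 2 serves the objective on implementation barriers and enablers, and its results feed the case studies in Study 3. If a consequence were reported as an enabler, plans for translation and dissemination could be built partly on an effect running the other way.

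**Working it through.** No arithmetic applies. The article gives no sample size, power, significance level or effect size for Study 2, and the point depends on none of them. The check sets the relevant sections side by side.

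1. **Aim against analysis.** The Aim and the Abstract speak of correlation. The Analysis speaks of influence on the primary outcomes and of drivers of use. This gap is visible without any assumption about timing.

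2. **What the directional words apply to.** For the trial outcomes the word is influence. Drivers refers to "important drivers of use of the intervention in routine practice", not to the trial outcomes. The dependent variables in the model are the primary outcomes, so a statement about use is a further step of interpretation.

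3. **When the predictors were measured.** The Study 2 Methods date three service characteristics at randomisation. That sentence does not cover the surveys, and no baseline survey is mentioned elsewhere. Under Trial status, data collection is still underway, while the Background already reports trial results for 38,725 people from the 60 services. The Discussion puts most collection late or post-trial. Ethical considerations describes survey consent in the future tense, but this is weak evidence, because the items collected at randomisation are also in the future tense. Late measurement is a reasonable inference. It is not stated.

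4. **What could have changed the scores by then.** In the intervention arm, the tools and the peer ranking. In the usual care arm, Study 1 allows services to take up the intervention after the trial, so a late survey there could also follow exposure in services that chose it.

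5. **What the model does about it.** The surveys cover both arms at 60 sites. With arm absent from the listed covariates, a difference in scores caused by the intervention and a difference in outcomes caused by the intervention would appear together as an association between score and outcome. Adding arm removes that route. It does not remove the route from a site's own results to its scores, which is why the wording matters as well as the model.

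6. **What the limitation covers.** Late collection is acknowledged, but only as a loss of early-adoption insight. The possibility that scores follow outcomes is not raised.

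**The case against.** The strongest reply is that late measurement is not documented. The limitation speaks of the majority of data across four studies. Interviews, video ethnography and the post-trial extraction could make up that majority by themselves, so the sentence does not date the surveys. Collection toward the end of the trial could also precede outcome extraction. A condensed article may leave survey scheduling to the full protocol, and its covariate list may be abbreviated. This stands in part. A reader might infer that the scores were certainly measured after the outcomes, but the document does not show that, and an early survey is not excluded.

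A reader might also infer that the plan treats climate and satisfaction as drivers of the trial outcomes, or that the bias must overstate the association. Neither is supported. Drivers refers to use of the intervention and is qualified by the words if any. No direction of bias can be established, since feedback could raise or lower scores.

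It is also fair that the stated aim is correlational, that influence is common regression phrasing, and that the explanatory sequential design uses the qualitative work to interpret the quantitative results, so the regression is not the only basis for conclusions. These points reduce the harm. They do not justify the directional wording, and a later analysis plan cannot make a late survey precede outcomes already collected.

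**Conclusion.** The concern holds in limited form. The Analysis section claims more than the aim, no pre-intervention survey is stated, the listed model has no term for arm, and the limitation on timing does not cover reverse causation. Whether the scores were in fact affected depends on two things the document does not settle: that the surveys were taken after the intervention began, and that the intervention, its feedback or the site's results changed climate or satisfaction. The first is likely from the text and the second is plausible. The size and direction of any distortion cannot be quantified from the document. This is a change worth making before analysis starts. It is not a demonstrated error in the data.

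**What to change.** - Record the date of each survey relative to randomisation and to outcome extraction, and report it.
- Before modelling, compare TCI and job satisfaction scores by randomised arm. A difference may show that the intervention affected them, but it does not prove this, because staff response may differ between arms.
- Include trial arm and its interaction with the scores in the multilevel model. Score information comes from at most 60 services, so the interaction may be imprecise and should be read with its confidence interval.
- Unless the surveys preceded the intervention, replace influence with association, in line with the aim, and add possible reverse causation to the limitations.
- Treat any use of the scores to predict later change in Study 1 as exploratory, and restrict it to services surveyed before the post-trial period began. Study 1 extracts post-trial data only from services that expressed interest in using the intervention, so this is a selected group.

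The cost is a few additional analyses on data already being collected, and a weaker claim about climate and satisfaction. Under Trial status, quantitative analysis had not commenced, so these steps could still be prespecified at that point.
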